### Outcomes

All outcomes will be evaluated on a timeframe of 2–12 months depending on the period between the day of hospitalization (inclusion visit) and the MD consultation (final visit of the study).

The primary outcome will be:Rate of controlled BP in MD consultation by office BP measurement

According to the European and International guidelines, the protocol for office BP measurement will be 5 min rest, 3 measurements at 1-min intervals in a supine position followed by 3 standing measurements at 1-min intervals for orthostatic hypotension test [1–4]. Unattended office BP measurement will be conducted by a supervisor (usually a nurse), who will explain the protocol to the patient before letting him rest in a quiet room: an automatic sphygmomanometer that will print the measurement statement at the end of the monitoring session. BP level will be estimated by the average of the last two BP measures in the supine position. BP will be considered as controlled with systolic BP < 140 mmHg and diastolic BP < 90 mmHg [1–4].

As a reminder, only the BP level by office BP measurement during the MD consultation (final visit of the study) will constitute the primary outcome.

The secondary outcomes will be:Rate and quality of home BP monitoring brought to MD consultation.

According to the 2020 International Society of Hypertension (ISH) Global Hypertension Practice Guidelines, the protocol for home BP monitoring will be 3-day monitoring with a cycle of 3 measurements every morning and every evening at 1-min intervals, in a sitting position, after 5 min of rest and before meals [1]. Quality will be assessed by the number of measurements (18 measurements over 3 days).2)Therapeutic adjustments (and their indication(s)) will be collected in the medical file due to the traceability of the prescriptions of antihypertensive treatment and the APN intervention report.3)Difference in rates of controlled BP between day hospitalization and MD consultation in each group. Note that BP level during day hospitalization is measured with the same protocol as during MD consultation.

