### Data collection

All data will be collected on-site, none remotely.

The main criterion will be measured in the framework of a protocol detailed in the “Outcomes” section, supervised by a healthcare giver (usually a nurse), using an automatic sphygmomanometer that can print the statement of measures at the end of the monitoring.

As for the home BP monitoring, even if it is conducted by participants at home, data will be collected on-site during the MD consultation.

Information about therapeutic adjustments will also be collected on-site in medical files.

All information required by the protocol will be recorded on a case report form. An explanation will be provided for any missing data. The data will be collected as obtained and clearly transcribed on the case report form.

Erroneous data found on the case report form will be deleted and the corrected data will be copied, next to the deleted information, accompanied by the initials, the date, and any justification by the investigator or authorized person having made the correction.

The chief investigator and the coordinator will make the final decision to terminate the trial.

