### Statistical analysis

Data scientists will remain blinded by means of two databases:One database for all the participants with the data of the day hospitalization and the MD consultation (including the primary outcome). To maintain blinding, the groups will be called “group A” and “group B”One database with only the data of the APN intervention, so as to perform statistical analysis specific to this stage

The primary outcome measure (difference in rate of controlled BP between “intervention” and “usual care” groups) will be analyzed using a chi-square test. A *p* value < 0.05 will be considered significant. Participants with missing data for this primary outcome will be excluded.

For secondary outcome measures, the rate of performance and quality of the home BP monitoring between the “intervention” and “usual care” groups will be analyzed using a chi-square test. The difference between average BP at baseline and at follow-up will be determined for all the patients and separately for patients in the two study groups. Differences between baseline and follow-up will be tested for significance within paired *t*-tests within each group. Proportions of therapeutic adjustments and their indications between the “intervention” group and the “usual care” group will be tested for significance using a *t*-test for independent samples. For these secondary outcomes, missing data will be replaced by the mean and the standard deviation calculated on the sample, in case of quantitative variables, and neglected for the qualitative variables.

Non-adherent participants (APN intervention missed for the “intervention” group) will be considered in the statistical analysis: the rate of non-adherent participants will be mentioned in the results.

No adjustment for baseline differences is scheduled following the randomization. Nevertheless, statistical analysis may highlight participant characteristics, which we can correlate to controlled BP. If needed, an adjustment for baseline differences will be performed at a later time.

Correlations between the performance and quality of home BP monitoring in MD consultation and controlled BP will also be analyzed.

No interim analyses are scheduled.

Statistical analysis will be carried out using the R software.

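### Replacing missing quantitative secondary values by the sample mean and SD understates the standard errors of the BP-change tests, and the plan does not say how an absent home BP sheet is scored

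*Protocol article*

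**What the plan says.** The Statistical analysis section has two missing-data rules.

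- **Primary outcome:** "Participants with missing data for this primary outcome will be excluded".
- **Secondary outcomes:** the rule is that "missing data will be replaced by the mean and the standard deviation calculated on the sample, in case of quantitative variables"; gaps in qualitative items are simply left out.

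The quantitative analysis clearly exposed to the second rule is BP change: "Differences between baseline and follow-up will be tested for significance within paired" t-tests, run within each group.

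Home BP monitoring is a secondary outcome, defined in the Outcomes section as "Rate and quality of home BP monitoring brought to MD consultation". On quality, that section says: "Quality will be assessed by the number of measurements (18 measurements over 3 days". The Data collection section says of home BP that "data will be collected on-site during the MD consultation". The planned comparison is that "the rate of performance and quality of the home BP monitoring between the “intervention” and “usual care” groups will be analyzed using a chi-square test".

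Nowhere does the protocol say how a standard deviation can stand in for a value, whether the sample is one arm or both, or how a patient who attends without a sheet is scored. It makes no allowance for imputation uncertainty.

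**The concern.** A value filled from the other patients carries no new information, but the t-test counts it as a full observation. The sample size stays at its full value while the spread shrinks (mean filled in) or is only copied (random draw). The standard error is then too small and the p value too low. This is a rule the protocol fixes, not a detail left to a later plan.

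The rule also treats one reading in two ways. Office BP at the MD consultation supplies both the primary outcome and the follow-up BP. If it is missing, the patient is excluded from the first analysis but given an invented value in the second. The reasons for missingness include an acute cardiovascular event, a dropout criterion under Participants. Nothing suggests that such patients have average BP.

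For home BP quality, an absent sheet at an attended visit is itself the non-adherence that the objective asks about. Handling it as a missing number would hide it in the quality measure.

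**Working it through.** **Inputs.** The protocol attaches no figure to this rule, so there is none to reproduce. The only missingness figure is the 10% loss margin under Sample size: 300 × 1.10 = 330, or 165 per arm. The 20% figure, the baseline/follow-up correlations and the home BP shares below are assumptions.

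**Step 1: formula, mean filled into the change score, arm's own mean.** With o of N values observed and observed SD s:

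- complete-case SE = s/√o
- SE after filling = s·√[(o−1)/(N−1)]/√N
- ratio = √[(o−1)/(N−1) × o/N], close to 1−m for a missing share m
- rejection rate of a nominal 5% test ≈ 2·[1−Φ(1.96 × ratio)]

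N = 165, o = 149 (10% missing): ratio = √(148/164 × 149/165) = 0.903, rejection rate 7.7%.

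N = 165, o = 132 (20% missing): ratio = √(131/164 × 132/165) = 0.799, rejection rate 11.7%.

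This is the upper end of the range. Baseline BP is taken at inclusion, so usually only the follow-up value is missing.

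**Step 2: simulation over the possible readings.** 20,000 runs per setting, 165 per arm, values missing completely at random, no true change in either arm, baseline/follow-up correlation 0.3 to 0.7. Monte Carlo standard error is at most about 0.2 percentage points.

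| What is filled | Sample used | Mean, 10% missing | Mean, 20% | Random draw, 10% | Random draw, 20% |
|---|---|---|---|---|---|
| Change score | Arm | 7.5–7.7% | 11.6–12.1% | 7.3–7.4% | 10.1–10.8% |
| Change score | Both arms | 6.3–6.4% | 8.2–8.5% | 6.0–6.3% | 7.5–8.0% |
| Follow-up BP only | Arm | 6.3–6.4% | 7.7–8.0% | 6.0–6.2% | 7.0–7.4% |
| Follow-up BP only | Both arms | 5.7% | 6.3–6.4% | 5.5–5.8% | 5.8–6.3% |
| Nothing (observed pairs) | – | 4.9–5.0% | 4.9–5.2% | – | – |

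Every reading exceeds 5%. A random draw reduces the excess but does not remove it.

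**Step 3: a mean taken over both arms.** If the true arm means are a and b and a share m is missing in each, the filled means differ by (1−m)(a−b). At 10% missing, a between-arm contrast loses 10% of its size. The table assumes a = b.

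**Step 4: home BP quality, illustration.** Assume 60% and 80% of patients bring a sheet, with 16 readings on each.

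- Absent sheet scored 0: 0.60 × 16 = 9.6 and 0.80 × 16 = 12.8, difference 3.2.
- Absent sheet given the mean: 16 in both arms, difference 0.
- Rate outcome, taking 150 per arm: 90/150 against 120/150. Chi-square = 0.20²/(0.70 × 0.30 × 2/150) = 0.04/0.0028 = 14.3, p = 0.0002.

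**The case against.** The strongest reply is that little depends on these tests. The primary analysis excludes missing cases, missing qualitative variables are neglected, and the tests clearly exposed are within-group comparisons that make no claim between arms. At the protocol's own 10% margin the excess is roughly half a point to three points. All of this stands and limits the severity.

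A second reply is that the wording includes the standard deviation, so a random draw may be meant and the filled values would then have spread. That is a fair reading, but the table shows that the error rate still exceeds 5%.

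A third reply concerns home BP. A reader might infer that the rule certainly gives an average count to patients without a sheet, and so erases the effect on adherence. The protocol supports neither step. Quality can be read as describing only the sheets brought, and the planned chi-square test suggests that the count may be categorised, in which case missing values are neglected. Non-bringers are also captured by the separate rate outcome, which in the illustration detects the difference clearly. The zero difference in quality arises because both arms were assumed to average 16 readings among bringers; comparing only the sheets brought would give zero too. What remains is an unstated scoring rule.

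**Conclusion.** The concern holds for the standard errors. As written, the rule makes the within-group paired t-tests of BP change anti-conservative: about 5.5 to 8% instead of 5% with 10% missing, and about 6.5 to 12% with an assumed 20% missing when the mean is filled in (a random draw runs slightly lower, from about 6%). The position within each range depends on whether follow-up BP or the change score is filled, and from which sample. The figures rest on values missing completely at random, no true change, and correlations of 0.3 to 0.7.

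A reader might take the upper figures of about 8% and 12% as the effect of the rule. They apply only if the change score is filled with the arm's own mean, which the protocol does not specify.

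For home BP quality, the finding is an ambiguity to resolve, not a demonstrated loss of the adherence result. The primary outcome is untouched. Severity: should be fixed.

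**What to change.** In the Statistical analysis section:

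1. Delete the replacement by mean and standard deviation.
2. State that BP change is analysed on patients with both baseline and follow-up office BP, reporting the number in each arm. If imputation is wanted, use multiple imputation within arm from baseline BP, with variances combined across imputations.
3. State that home BP monitoring not brought to an attended MD consultation is scored as 0 of 18 (not performed) and never receives an imputed mean. A patient who does not attend the MD consultation remains missing.

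The planned paired t-tests and chi-square tests can stay; this defect does not require other tests. The cost is a few sentences and standard R code, with no change to trial conduct. The price is slightly wider intervals on secondary outcomes. Observed pairs hold 5% under missingness completely at random; if dropout is related to BP they may be biased, and the mean replacement would not cure that either.

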### Participants

The patients will be recruited during their visit to the day hospitalization section of the Diagnosis and Therapeutic Center of Hôtel-Dieu University Hospital, for hypertension-related complications and cardiovascular risk assessment as part of their hypertension management.

Participants will be eligible if they are at least 18 years of age, diagnosed with hypertension (treated or untreated), followed by a MD in the structure for hypertension management, and able to provide written informed consent. Hypertension is defined by BP ≥ 140/90 mmHg by office BP measurement and/or BP ≥ 135/85 mmHg by home BP monitoring.

The non-inclusion criteria will be patients under 18 years old, APN follow-up prior to day hospitalization, pregnancy, guardianship/curatorship, or inability to give free informed consent.

Written information and oral explanations will be given to patients. To complete their inclusion in the study, free informed and written consent will be collected from each participant during the day of hospitalization.

The dropout criteria will be an acute cardiovascular event during the study period and/or therapeutic adjustment of hypertension treatment by another health professional than the APN or MD referent during the study period and/or refusal to proceed in the study.

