### Sample size

For primary outcome measurement, according to the preliminary results of our pilot study, we estimated the number of patients to be included in our trial. We made the hypothesis of 50% and 65% of controlled BP in the “usual care” and “intervention” groups, respectively, equivalent to a 30% increase in the rate of controlled hypertensive participants in the “intervention” group (corresponding to a 15% absolute increase or a 30% relative increase in the controlled BP rates). Assuming an equal number of patients in the two groups, a chi-squared test with a 2-sided significance level of 5%, and a power of 85%, it will be necessary to recruit 300 patients (150 per arm). With a 10% margin of loss to follow-up, 330 patients will need to be recruited (165 per arm).

Sample size calculation was performed with the SAS software (version 9.4; Institute Carry, NC).

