### Sequence generation

Block randomization will be conducted by [name], a MD in the unit trained in biostatistics, using the randbetween formula (0 to 100) on the Excel software for Windows, by blocks of variable size. The even numbers will constitute the “intervention” group and the odd numbers the “usual care” group. This method will ensure the homogeneity and unpredictability of the randomization during the study period. No stratification is scheduled.

The randomization list will then be copied onto a permanent registry. Allocation groups will be concealed in individual numbered opaque sealed envelopes (one per participant). The number and allocation for each envelope will be assigned according to the randomization list.

The individual sealed envelopes will be given to the day hospital nurses who will randomize participants. Nurses will never have access to the randomization list.

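### The primary chi-square is valid but leaves same-protocol baseline BP unused, and the plan leaves any later adjustment unspecified

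*Protocol article*

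**What the plan says.** In the protocol article, the Statistical analysis section says that the between-arm difference in the rate of controlled BP "will be analyzed using a chi-square test", with significance at p < 0.05. On covariates it says "No adjustment for baseline differences is scheduled following the randomization". Two sentences follow: "Nevertheless, statistical analysis may highlight participant characteristics, which we can correlate to controlled BP", and then "If needed, an adjustment for baseline differences will be performed at a later time". No covariate, model, criterion for need, or status of the adjusted result is given.

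Other sections bear on this:

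- Outcomes, on the baseline measurement: "Note that BP level during day hospitalization is measured with the same protocol as during MD consultation". Baseline BP serves only to describe change from day hospitalisation to the MD consultation. The Statistical analysis section tests that change within each group by paired t-tests.
- Participants: eligible patients are those "diagnosed with hypertension (treated or untreated", so BP at entry can vary widely.
- Sequence generation: "No stratification is scheduled".
- Sample size: 50% versus 65% controlled, two-sided 5%, 85% power, 150 evaluable per arm.

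**The concern.** The endpoint is office BP at the final visit, cut at 140/90 mmHg. The same quantity, measured in the same way, is available before randomisation and sits in the same database as the primary outcome. It is a natural covariate, and neither the randomisation nor the between-arm test uses it. Where it predicts final control, the unadjusted comparison is less precise than it could be at no extra cost in data.

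The second issue is the order of events. The text foresees looking for characteristics associated with the outcome and then adjusting if that seems needed. An adjusted estimate reached in this way has covariates selected from the trial's own results. If it differs from the chi-square result, a reader cannot tell how much of the difference comes from the selection.

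**Working it through.** **1. Inputs.** From the Sample size section: p0 = 0.50, p1 = 0.65, two-sided alpha 0.05, 150 per arm. The correlation rho between baseline and final BP is not in the documents. It is assumed over 0.3 to 0.7.

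**2. The plan's own figure.** With pooled variance under the null and mean rate 0.575:

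- Null term: 1.960 × √(2 × 0.575 × 0.425) = 1.960 × 0.6991 = 1.370.
- Alternative term: √(0.25 + 0.2275) = 0.6910.
- n per arm for 85% power = (1.370 + 1.036 × 0.6910)² / 0.15² = 194, not 150.
- Power at 150 per arm = Φ[(0.15 × √150 − 1.370) / 0.6910] = Φ(0.676) = 75.0%.

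The stated 85% is therefore not reproduced. The starting point for any gain is about 75%.

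**3. Power with baseline BP in the model.** Simulation with 150 per arm: bivariate-normal baseline and final BP, final control 50% versus 65%, and 50% controlled at baseline (an assumption that matters only for the yes/no column). Each cell uses 6,000 trials, so Monte Carlo error is about half a point. The adjusted test is the arm coefficient in a logistic regression with one baseline BP variable.

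| Assumed rho | Chi-square | Adjusted, baseline control yes/no | Adjusted, continuous baseline BP |
|---|---|---|---|
| 0.3 | 76% | 77% | 77% |
| 0.4 | 76% | 78% | 79% |
| 0.5 | 76% | 80% | 82% |
| 0.6 | 77% | 82% | 85% |
| 0.7 | 76% | 86% | 89% |

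A second, independent run with continuous BP gave about 78, 79, 82, 85 and 90%.

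**4. Cross-check by formula.** With both margins near 50%, the correlation between yes/no control states is r = (2/π) × arcsin(rho), and the effective n per arm is about 150 / (1 − r²).

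- rho 0.3: r = 0.19, effective n = 156, power about 77%.
- rho 0.5: r = 0.33, effective n = 169, power about 80%.
- rho 0.7: r = 0.49, effective n = 198, power about 86%.

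These agree with the yes/no column. Read the other way, yes/no correlations of 0.3, 0.4 and 0.5 (power 79, 82 and 86%) need underlying BP correlations of about 0.45, 0.59 and 0.71. The two scales must not be confused.

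**5. The open adjustment.** Under no effect, 10,000 simulated trials per value gave about 5.7% rejection for the chi-square and 5.0% for the adjusted test. If whichever of the two was significant could be claimed, rejection would be about 6.5% (rho 0.3), 7.3% (0.5) or 8.3% (0.7). This shows what an unrestricted choice would cost. The plan does not state such a choice.

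**The case against.** The case for leaving the plan alone is substantial. The chi-square is one named test at one threshold, with no interim look, and it matches the test in the Sample size section. In a randomised trial it is unbiased without adjustment.

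A reader might infer that chance imbalance in baseline BP distorts the result. With 50% controlled at entry, the 95% range of imbalance is ±1.96 × √(2 × 0.25 / 150), about 11 points. At a yes/no correlation of 0.4, an imbalance of that size moves the difference by about 4.5 points. That is ordinary sampling error, already covered by the test; it is a loss of precision, not bias.

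A reader might also infer that the primary p value is open to choice, so that the 6.5-8.3% above is the trial's error rate. The text does not support this. Adjustment comes later, and nothing lets it replace the primary test. The analysts also see the groups only as A and B, which reduces the risk but does not fix covariates in advance.

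The gain may be small. The documents give no correlation and do not show that baseline BP is the strongest predictor. The APN intervention section foresees treatment changes during the day hospital session, which could weaken the link.

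Finally, this is a condensed article, and covariates are often left to an analysis plan. That answers a complaint about missing detail. It does not answer a stated decision to omit baseline adjustment, followed by a stated intention to adjust if needed. Lack of stratification is a legitimate choice in a single-centre trial and is not criticised here.

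**Conclusion.** The point stands as an avoidable loss of precision and a loosely worded clause, not as an error in the primary test. The benefit of adjusting for continuous baseline BP at 150 per arm ranges from about 1-2 points of power at a correlation of 0.3, through about 6 points at 0.5, to about 13-14 points at 0.7. These figures rest on an assumed correlation and a bivariate-normal model with one baseline BP variable. They were obtained for a logistic-regression test, not for the standardised risk difference itself.

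The integrity risk is confined to an added or preferred adjusted result. It would be tempting to present adjustment as the cure for the gap between about 75% and the stated 85% power. The documents do not support that: the gap comes from the sample size calculation, and only a correlation of about 0.6 or more would close it.

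**What to change.** Before any outcome is examined by group, amend the Statistical analysis section as follows.

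- Prespecify a comparison of controlled BP by arm adjusted for day-hospitalisation supine systolic and diastolic office BP, both continuous. Logistic regression with standardisation over the trial population would do.
- Report the marginal risk difference with its 95% CI. This keeps the 15-point absolute difference as the target; the model's conditional odds ratio would not.
- Keep the unadjusted chi-square alongside it, and state in advance which of the two carries the primary conclusion. The precision gain counts towards that conclusion only if it is the adjusted analysis.
- Delete the if-needed clause, or label any further adjustment exploratory.
- Do not add time to the MD consultation unless the planned interval is recorded before the envelope is opened. The APN intervention section says the MD visit is set first by usual management, but the Randomization and Allocation concealment sections have appointments booked after allocation is known. The interval therefore cannot be assumed to be a baseline variable.

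The cost is a few sentences and a little R code. Baseline BP is already collected, so no new data are needed. The sample size shortfall needs its own correction.
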